### Randomisation

Once eligibility is confirmed, the consent process completed, and screening data entered into the trial database, participants will be sent a text/email, generated by the Peninsula Clinical Trials Unit (PenCTU), requesting them to complete the baseline questionnaires. Once complete, the participant will be randomly allocated on a 1:1 ratio, using random permuted blocks, stratified by centre and presence/absence of lumbo-pelvic pain pre-pregnancy, to either the standard care or intervention group (figure 1). Screening data capture and randomisation is achieved via a web-based system created by the PenCTU.

After randomisation, a series of emails will be automatically generated. A blinded email will be sent to the research team members involved in eligibility screening. An unblinded email will be sent to the chief investigator (CI), study administrator and site principal investigator (PI). An email/text will be sent to the participant to inform them of their group allocation.

### Blinding

The trial participants and NHS treating physiotherapists are unable to be blinded due to the nature of the intervention. Every effort will be made to ensure the research team is blinded to group allocation throughout the trial. The statisticians will remain blind to group allocation when conducting the primary analyses until analyses that necessitate unblinding need to be performed, such as wear-time analysis. The research team will keep a detailed log of any inadvertent unblinding events. Final unblinding of the research team will occur after database lock and blinded analysis has been undertaken.

### Interventions

NHS physiotherapists will provide all interventions at the two protocolised video-based sessions. At the participant’s preference, face-to-face sessions can be undertaken in place of these remotely delivered sessions. The initial session will last a maximum of 60 min and the follow-up session (a maximum of 30 min) will be scheduled approximately 10 days later. Participants are not prevented from receiving other care. This will be captured in the health resource use questionnaire.

#### Standard care group (standardised information and exercise)

The standard care regime was designed in collaboration with women’s health physiotherapists experienced in the treatment of persistent PGP. This was considered by them to be reflective of usual clinical practice. It comprises two components:

##### Standardised information

This will be provided through a discussion centred on the publicly available booklet produced by the pelvic, obstetric and gynaecological physiotherapy special interest group ‘Guidance for mothers-to-be and New Mothers: Pregnancy-related Pelvic Girdle pain’ (https://pogp.csp.org.uk/system/files/pogp-pgppat_3.pdf).

##### Standardised exercise

The physiotherapist will teach participants a programme of up to four lumbo pelvic/hip exercises, typical of those provided within usual physiotherapy practice. These will be selected from a protocolised set (online supplemental file 1), on the basis of their initial assessment. Participants will be advised to complete the exercises on 3 days of the week, with each session lasting approximately 20–30 min. All participants will receive an exercise leaflet describing the exercises, with accompanying images. This will be posted or emailed dependent on participant preference.

10.1136/bmjopen-2022-063767.supp1Supplementary data

#### Intervention group (standardised information and exercise plus DEFO)

In addition to standard care, participants allocated to the intervention group will be provided with two pairs of customised DEFOs (figure 2, DM Orthotics, https://www.dmorthotics.com). The orthosis will be worn for the first time at the initial intervention session, enabling the physiotherapist to check the fit; this will also be reviewed at the follow-up session. Participants will be advised to wear the DEFO for a maximum of 12 hours per day, with wear time graduated over the course of the first 5 days in line with manufacturer guidance. The orthoses are delivered with an advice booklet detailing donning and doffing, wear time and care instructions, with a supplementary video hosted on the trial web page. Where alterations are required because of poor fit, in line with current practice the NHS physiotherapists will follow a standard operating procedure, making contact with the orthotic company to arrange an adjustment if required.

**Figure 3 F3:**
[figure not shown]
Pelvic girdle pain screening battery. PGP, pelvic girdle pain; SIJ, Sacro Iliac Joint.

### Data collection

#### Feasibility outcomes

The trial outcomes include feasibility and acceptability of the EMaPP trial. Quantitative and qualitative feedback will be obtained to identify the main determinants of experience and acceptance of the trial in line with the trial objectives. In particular, the following measures and operational criteria will be determined:

Number and proportion of eligible participants from the target population.Willingness of participants to be randomised.Recruitment and retention rates of eligible participants through the trial.Completeness of data sets/outcome measures.Incidence of face-to-face sessions.

#### Clinical outcome measures

A battery of standardised, patient reported outcome measures, together with demographic and diagnostic characteristics (birth details, pain history, Beighton Score^20 21^ and two point estimation (2PE) Task,^22 23^ will be collected at baseline. A selection of outcome measures will be repeated fortnightly and at 12 and 24 weeks after the first-intervention session to map in more detail the trajectory of pain over the trial timeline (table 2). All patient reported outcome measures will be reported directly by the participants via the web-based application. At each time point, participants will automatically receive five text/email reminders (one per day) if the data entry has not started. All patient reported outcome measures included within this study align with the PGP core outcome set for evaluating the effectiveness of interventions in postpartum PGP.^24^

**Table 2 T2:** Assessment schedule

Assessments	Baseline	Post-initial appointment		
		Fortnightly	12 weeks	24 weeks
Demographics, birth details, pain history	x			
Beighton score^20 21^ to determine joint hypermobility	x			
Two-point estimation task^22 23^ to determine implicit somatoperception	x			x
Pain medication use	x	x	x	x
Numerical Pain Rating Scale^25 26^	x	x	x	x
Health and Social Care Resource use Questionnaire to collect data on health, social and wider care resource use^18^	x		x	x
Edinburgh Post-natal Depression Scale^33^ to assess post-natal depression (cut-off **≥**12 points)	x		x	x
Freemantle Back Awareness Questionnaire to assess explicit body perception of the lumbo-pelvic region^36 37^	x		x	x
Pelvic Girdle Questionnaire^40^ to assess function and symptoms	x		x	x
Short-form 36^41^ to assess health-related quality of life and calculate quality adjusted life-years (QALYS)	x		x	x
EQ-5D-5L to assess health-related quality of life and calculate QALYS^42^	x		x	x
International Consultation on Incontinence Questionnaire, Urinary Incontinence—Short Form to assess level and impact of symptoms of incontinence^43^	x		x	x
Tampa Scale Kinesiophobia to assess fear of movement/kinesiophobia^44^	x		x	x
Wear-time adherence (Orthotimer)				x
Qualitative interviews				x

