### Eligibility screening process

Eligibility screening will occur via a two-stage process. On receipt of the completed reply form a telephone screen (stage 1) will be undertaken using a pre-formatted screening checklist based on the eligibility criteria. If deemed eligible, a video conference physical screening assessment will be arranged (stage 2). A screening pack will be sent out ahead of this physical screening appointment containing: the screening battery tests (schema of physical tests and instructions), Beighton self-report score, trial consent forms, orthotic measuring guide and tape measure (to capture measurements for production of the customised orthosis, should the participant be allocated to the intervention group) and digital callipers.

The physical screening requires the presence of a partner/trusted other to assist with the physical assessment and orthosis measurements, under the guidance of the remote researcher. All screen failures will be recorded.

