### Intervention fidelity

NHS clinicians will complete a pre-formatted intervention fidelity checklist for each of the two physiotherapy sessions. Adherence to wearing the orthosis will be assessed via a temperature sensor integrated into the seams of the orthosis. The Orthotimer sensor (Rollerwerk Medical Engineering, Balingen, Germany) is embedded in a small (13 mm×9 mm×5 mm), dust and watertight unit. It will record time, date and temperature every 15 min over the 24-week period with temperature precision of ±0.1°C. DM Orthotics will activate and sew the sensor into each orthosis before dispatching to participants. Adherence to the home exercise programme is not assessed during the trial, however it is explored via the qualitative interviews.

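### Follow-up is timed from the first intervention session, which in the orthosis arm alone must wait for manufacture and delivery, so the time from randomisation to the 24-week endpoint can differ between arms

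*Protocol article*

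**What the plan says.** **Order of events.** Under Randomisation, baseline questionnaires come first, and then: "Once complete, the participant will be randomly allocated on a 1:1 ratio". No intervention session has taken place by then.

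**Time origin of follow-up.** Under Clinical outcome measures, the repeat assessments "will be repeated fortnightly and at 12 and 24 weeks after the first-intervention session". Table 2 uses the same origin in its column heading, "Post-initial appointment". The text and the table agree, so this is a stated choice.

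**What the first session needs in the orthosis arm.** Measurements are taken at screening "to capture measurements for production of the customised orthosis, should the participant be allocated to the intervention group", so production follows allocation. Under Intervention fidelity, "DM Orthotics will activate and sew the sensor into each orthosis before dispatching to participants". Under the Intervention group heading, "The orthosis will be worn for the first time at the initial intervention session, enabling the physiotherapist to check the fit".

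**What the first session needs in the standard care arm.** It needs a booked physiotherapy session with a booklet and exercise teaching. No manufactured item is involved.

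**Where the 24-week value is used.** The Quantitative section focuses on change in day-time pain at 24 weeks. Table 3 includes an efficacy criterion based on whether an 80% CI makes a difference of at least 1 NRPS point plausible.

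**The concern.** Randomisation makes the arms comparable at randomisation and at fixed times after it. Here the clock starts at a later event whose timing depends on the arm. If the orthosis adds a wait, that arm's 24-week score is taken later after baseline than the standard care score. Any background change in pain during the extra time then appears as a between-group difference. It favours the orthosis if pain tends to ease with time and counts against it if pain tends to worsen.

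Three results are exposed:
- the between-group difference in pain change, and through it the efficacy criterion;
- QALYs over the follow-up period, if that period is counted from baseline;
- the 12- and 24-week data of anyone randomised who never has a first session, since on the article's wording no date is fixed for them and no imputation is planned.

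The trial is meant to inform a definitive RCT, so an arm-dependent time zero could also be carried forward.

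**Working it through.** **1. The plan's own figures.** N = 60, from Sample size. The half-width of a 95% CI for a proportion is 1.96 × √(p(1−p)/60).
- p = 0.5: 12.7 points (stated as about 13).
- p = 0.8: 10.1 points (stated as 10).
- Followed up per group at 80% retention: 30 × 0.80 = 24 (stated as 24).

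All three reproduce, and none is disputed.

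**2. Is the time origin arm-dependent?** The chain in the orthosis arm is: baseline, randomisation, production, sensor sewn in, dispatch, first session (week 0). In the standard care arm it is: baseline, randomisation, first session (week 0). The production and dispatch steps occur in one arm only. The only session interval stated is about 10 days between the first and second sessions. No interval from randomisation to the first session is given for either arm.

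**3. Size of the shift (assumed inputs).** Let L be the extra weeks to the first session in the orthosis arm compared with standard care. If standard care starts at once, the orthosis arm's 24-week assessment falls 24 + L weeks after randomisation:
- L = 2: 26 weeks
- L = 4: 28 weeks
- L = 6: 30 weeks

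**4. Size of the artefact (assumed inputs).** Artefact = (background fall over 24 weeks ÷ 24) × L.
- Low corner: 0.5/24 × 2 = 0.04 points.
- High corner: 1.5/24 × 6 = 0.38 points.
- L = 0: 0 points.

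A more extreme corner, L = 8 with 0.10 points per week, gives 0.80. That slope means a fall of 2.4 points over 24 weeks, which is hard to square with pain that the Introduction calls recalcitrant.

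**5. Effect on the efficacy criterion (illustration).** Assumptions: 24 per arm, SD 2 (not in the article), and the criterion read as an upper 80% limit of at least 1 point.
- Standard error = 2 × √(2/24) = 0.577.
- Half-width = 1.30 × 0.577 = 0.75.
- An observed difference of 1 − 0.75 = 0.25 is then enough to pass.

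Normal-approximation chance of passing with no true effect:

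| Artefact | (0.25 − artefact)/0.577 | Chance of passing |
|---|---|---|
| 0 | 0.43 | about 33% |
| 0.04 | 0.36 | about 36% |
| 0.38 | −0.23 | about 59% |

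For SDs of 1.5 to 2.5, the chance is 16% to 47% with no artefact and 45% to 67% with an artefact of 0.38. A bias well below 1 point can therefore matter to this criterion.

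**6. Participants without a first session (illustration).** Suppose k per arm never attend and have no follow-up, 80% of the rest are retained, and all 60 stay in the denominator. Retention = (60 − 2k) × 0.80/60.
- k = 1: 77% (23.2 per arm)
- k = 3: 72% (21.6 per arm)
- k = 5: 67% (20.0 per arm)

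The 24-week completion band in Table 3 is amber from 60% to 80%, so none of these moves out of the band that 80% already occupies.

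**The case against.** **Unequal timing is not shown.** A reader might infer that the arms are in fact measured at different times. The article does not establish that. It gives no lead time, its flow chart is not reproduced in the text available, and standard care also waits for an NHS booking. If that wait matches or exceeds manufacture, or sessions are booked alike in both arms, the gap vanishes. This stands: the plan allows a difference and makes one likely, but does not prove one.

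**The magnitudes are assumed.** Neither the delay nor the trend comes from the article, and long-standing severe pain may change little. The extra wait also precedes the exercise programme, so a trend that owes something to standard care overstates change during the wait. This stands, and is why the size is a range starting at nil.

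**Non-attenders.** The missing due date is an inference from silence in a condensed article, and the full protocol or database may supply one. A reader might go further and say that retention is really measured among starters, or that non-attenders are excluded. The article does not support this: Sample size and Table 3 count participants as a whole, and outcomes are summarised by allocated group. Nor can it be said that adverse events would go uncollected, because that section describes fortnightly monitoring throughout the 24 weeks without tying it to the first session.

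**There is a reason for the chosen origin.** It gives everyone the same time since treatment start and matches the 24-week wear-sensor window. That is a fair argument for keeping wear time on the session clock. It does not protect a randomised comparison of pain.

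**Stakes are limited.** This is a feasibility trial without a power calculation, its results are not meant to guide clinical decisions, and the efficacy criterion has no red, amber or green threshold. This keeps the point moderate.

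**Conclusion.** The point holds as a design weakness with a cheap remedy. The article states a post-randomisation time zero that in one arm depends on a product being made and delivered. The interval from baseline and randomisation to the 24-week endpoint can therefore differ between arms, and the pain comparison may carry an elapsed-time component.

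Its size is unknown. Under an assumed extra delay of 2 to 6 weeks and an assumed linear fall of 0.5 to 1.5 points per 24 weeks in both arms, it is about 0.04 to 0.38 points. It is nil if first sessions fall equally late in both arms. No stated precision or sample size figure changes.

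The due-date gap for those without a first session is secondary and conditional on what the full protocol says. Such participants belong in the retention denominator as randomised.

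**What to change.** **From now on.** Time the fortnightly, 12-week and 24-week requests from randomisation in both arms, and record the date of the first session. If the session clock is kept, set a randomisation-based due date at least for participants who have no first session, and keep them in the retention denominator. Wear-time summaries can stay on the session clock.

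**For participants already on the session clock.** Report randomisation-to-first-session and randomisation-to-assessment intervals by arm. Alongside the session-anchored analysis, add one using the fortnightly NRPS value nearest 24 weeks from randomisation. With complete fortnightly reporting, that value lies within about a week of the target. In Table 2 only NRPS and pain medication are fortnightly, so the other questionnaires cannot be re-anchored in this way; for them the intervals are the safeguard.

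**Cost.** A protocol amendment and a change of trigger date in the web system, with N unchanged. Time since first wear at the randomisation-anchored endpoint is shorter by the manufacturing wait, which should be stated when the result is read. Two clocks must be reported for those already enrolled.

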#### Proposed clinical outcome measures

Numerical Rating of Pain Scale (NRPS) is the proposed primary outcome measure for the definitive RCT. This 0–10 point scale is widely used,^25^ quick to complete and with a format suitable for completion through a mobile/application. There is evidence in chronic pain patients to suggest a one-point change is clinically significant,^26^ and hence a difference between groups of >1.0 at 24-week follow-up will indicate a signal of efficacy. Participants will rate their pain experience over the past fortnight using the NPRS within four categories: (i) worst level of day-time pelvic pain, (ii) average level of day-time pelvic pain, (iii) worst level of night-time pelvic pain, (iv) average level of night-time pelvic pain.

The proposed secondary outcome measures are detailed in table 2.

Resource use and costs associated with delivery of both intervention arms will be estimated. Resource use associated with the measurement, ordering, delivery and production of the orthosis and the physiotherapy interventions, will be collected via within trial reporting, including participant level contact and non-contact time for NHS staffing input.

### Intervention fidelity

NHS clinicians will complete a pre-formatted intervention fidelity checklist for each of the two physiotherapy sessions. Adherence to wearing the orthosis will be assessed via a temperature sensor integrated into the seams of the orthosis. The Orthotimer sensor (Rollerwerk Medical Engineering, Balingen, Germany) is embedded in a small (13 mm×9 mm×5 mm), dust and watertight unit. It will record time, date and temperature every 15 min over the 24-week period with temperature precision of ±0.1°C. DM Orthotics will activate and sew the sensor into each orthosis before dispatching to participants. Adherence to the home exercise programme is not assessed during the trial, however it is explored via the qualitative interviews.

#### Adverse events

Throughout the trial, all possible precautions will be taken to ensure participant safety and well-being. Participants will be monitored for adverse events throughout the 24 weeks. The likelihood of participants being harmed by either wearing the orthosis or undertaking the exercise programme (which reflects usual clinical practice) or any of the trial procedures is considered very low. Collection and reporting of adverse events will be captured via the web-based app and relate to those classified as an adverse reaction (including adverse device effects) or those which are serious. These will be collected at fortnightly intervals. On receipt of a reported reaction or serious adverse event, the CI will contact the local PI to discuss causality. All adverse events will be reported at the Trial Steering Committee (TSC) and Trial Management Group (TMG) meetings.

#### Qualitative substudy

The aim is to explore the experiences of wearing (participant) and providing (clinicians) the pelvic orthosis and engaging in the trial procedures.

The specific objectives are to investigate acceptability of the trial methods across both arms, acceptability (comfort, wear time) of the orthosis, impact the intervention may/may not have on the participant’s life and adherence to the exercise regime.

Semi-structured telephone interviews will be undertaken, at the end of the trial, with 10 purposively sampled participants (n=5 intervention group, n=5 standard care group) and five NHS physiotherapists involved in delivering the interventions. A topic guide will be used (online supplemental file 2). Interviews will be digitally recorded and transcribed verbatim.

10.1136/bmjopen-2022-063767.supp2Supplementary data

Informal telephone exit interviews will be undertaken with participants that withdraw from the trial to share their reason for withdrawing. The interviews will not be recorded or transcribed. Field notes will be taken.

#### End of trial definition

There are no formal stopping criteria. It will be prematurely stopped on safety grounds through a decision by the TMG and TSC.

#### Sample size

As this is a feasibility trial, a formal sample size calculation, based on power for detecting a clinically meaningful between-group difference in a primary clinical outcome, will not be undertaken. The trial aims to recruit 60 participants over a 7-month period. The sample size is pragmatic and determined to be large enough to provide robust estimates on the likely recruitment rates and follow-up and estimates of the variability on the proposed primary outcome to inform a future sample size calculation. The target is set to enable determination of whether it would be practicable to recruit adequate numbers in a manner conducive to implementing a reasonably costed definitive trial. A sample size of 60 will allow overall retention rate at 6-month follow-up to be estimated to within a 95% CI of approximately ±13% (±10% if retention rate is 80%). Assuming a non-differential retention rate of 80%, this should provide follow-up outcome data on a minimum of 24 participants per group.

### PPIE

Women with experience of severe chronic PGP provided input into the study design. Priority of the research question, choice of outcome measures, recruitment methods and mode of intervention delivery were informed by discussions with women through a focus group session and ongoing discussions with a dedicated lay member of the project team. Lay input continues through membership on the TMG, and an additional independent lay member on the TSC. PPIE will play a key role in the dissemination of trial findings, contributing to and reviewing material.

